### Adverse event (AE) monitoring

Clinical AEs will be monitored throughout the study. Since the study procedures are not greater than minimal risk, serious AEs are not expected. If any unanticipated problems related to the research involving risks to individuals or others happen (including serious AEs), these will be reported to the institutional review board (IRB).

### Access to data

The principal investigators and co-investigators will have access to the final trial dataset. There are no limits to investigators by external agencies.

### Dissemination of data

Results of this study will be disseminated in full in professional journals, national, and international conferences. A lay summary of study results will be provided on ClinicalTrials.gov upon study completion. Plans for public access to data in an appropriate database will be developed.

### Protocol modifications

Although major protocol modifications are not anticipated at this point, any important modifications will be requested through a modification request form to the University of Kentucky’s Medical IRB and communicated to all study personnel.

### Authorship

Authorship will be granted to those who make notable contributions to the study.

## Discussion

Pediatric injury places children at significant risk for long-term impaired emotional and physical health [1, 2, 4, 5, 56]. While there is strong consensus that interventions to support injury recovery are essential and that better understanding intervention targets will increase effectiveness, interventions remain in their infancy and many have not been effective in promoting physical and emotional health [12, 57, 58]. Evidence suggests that adherence and coping may serve as key mechanisms of action for improving children’s post-injury health [18, 37, 59]. By partnering with parents [60, 61] and targeting children’s adherence and coping directly [18, 37, 59], the Cellie Coping Kit intervention is an ideal candidate for promoting full recovery in millions of children.

Building on promising findings from pilot studies [25], the current RCT goals represent an important next step in the advancement of the Cellie Coping Intervention for Injury. The strengths and potential positive outcomes of implementing a waitlist control RCT design with multiple informants are numerous. The current study design obtains data from both the child and parent perspective on physical recovery, emotional recovery, and response to the intervention. In addition, the design includes the physicians’ perspective on physical recovery and Cellie interventionists’ perspectives on intervention engagement / uptake. Combining data from multiple informants will provide rich information specific to the targets (i.e. adherence, coping behaviors, physical recovery, emotional health, HRQOL) and intervention engagement. Collecting data on cost, and on engagement from multiple perspectives (child, parent, and interventionist), will lay the ground work for more research on intervention dissemination and implementation. The longitudinal study design will allow us to examine change over time and investigate both short- and long-term effects of the intervention. Evaluating the level of support that a family needs to implement the Cellie Intervention is also a study strength. The role of the interventionist in this intervention has been designed so that advanced credentialing (i.e. licensure or certification) is not necessary. Rather, a wide range of health and behavioral healthcare workers can be trained to teach and support the use of the Cellie Coping Kit, facilitating implementation and sustainability of the approach. This is especially important in many rural healthcare professional shortage areas, where professionals with advanced degrees are in short supply, yet high demand. The design of this study will allow us to explore whether Cellie interventionists are necessary (Cellie intervention group) or whether the family can use the intervention with no additional instruction (waitlist group). The use of a waitlist control group will allow group comparisons at T2 and T3, with the additional possibility of examining intervention timing effects at T4. In addition, the waitlist design ensures that all participants will be offered the Cellie Coping Kit for Injury intervention addressing the overarching goal of the team to provide evidence-based resources to promote injury recovery. The target population of this study is also a strength. Much research on adherence/health to date has been conducted with chronic illness populations rather than injury [32–34]. Injury is in many ways qualitatively distinct from other health conditions in its treatment and long-term physical and emotional impact. In addition, this research protocol will include many families from rural communities, an underserved and under-researched population [62]. Including several strategies of collecting follow-up data (via phone, Internet, mail) will contribute to our understanding of how to engage and retain participants from rural communities at follow-up time points.

We recognize a number of potential limitations of this study design. Families may face some barriers to implementing the Cellie Coping Kit, such as difficulty understanding the materials or busy schedules interfering with the intervention. Thus, there may be variation in intervention usage within the intervention and waitlist control groups. We will address this by examining usage per child and parent report; however, the Kit’s portability and child- and parent-driven usage mean that it is not feasible to include behavioral observations to capture actual usage in the child’s environment. Other potential limitations include the possibility of lower than expected retention rates or logistical challenges (e.g. problems contacting participants by phone) that can arise in research with families living in rural communities. Any retention challenges will provide valuable information in planning for future research and intervention implementation. Other limitations of this RCT could include recruitment challenges and potential sampling bias. The research team will work to avoid such challenges by closely monitoring eligibility, recruitment, enrollment, and retention. Strategies will be adjusted as necessary to ensure recruitment goals are met and sample characteristics are reasonably balanced. Given the limited scope and funding for this pilot study, blinding will be limited; research staff and participants will be blind through the baseline assessment but not at subsequent follow-up assessments. To mitigate bias, research staff will be trained to follow a structured protocol to ensure all follow-up assessments are conducted in a similar manner. Because the medical team may directly observe intervention materials, it is not feasible to keep them blinded from study condition. Finally, this research design is a pilot study; thus, future research with a larger sample will be necessary to fully explore intervention effects.

In summary, the current waitlist control RCT aims to examine intervention feasibility and provide an initial estimate of impact. The data obtained in this study will support the larger program goal of using a translational research approach to develop an effective, low-cost mechanism for teaching adaptive coping strategies to children with injury and their families. If results suggest that the intervention helps promote physical and emotional health among children after experiencing an injury, then the Cellie Coping Intervention could be a low-cost mechanism to disseminate evidence-based strategies to support recovery from injuries in medical settings. The accessibility and user-driven design of the intervention makes it ideal for distribution across diverse settings and individuals. If shown effective in children with injury, there may also be avenues for broader application across other pediatric medical conditions.

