**Method / Design:**

Eighty children (aged 8–12 years) and their parents will complete a baseline assessment (T1) and then will be randomly assigned to an immediate intervention group or waitlist group. The Cellie Coping Kit for Injury Intervention will be introduced to the immediate intervention group after the T1 assessment and to the waitlist group following the T3 assessment. Follow-up assessments of physical and emotional health will be completed at 6 weeks (T2), 12 weeks (T3), and 18 weeks (T4).

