Following caregiver consent and child assent, participants will complete a baseline assessment (T1) including measures of coping, HRQOL, and psychological symptoms. Families will then be randomized to the immediate Cellie Intervention (*n* = 40) or Waitlist control (n = 40). Those in the intervention condition will begin the intervention immediately: Cellie interventionists (trained research assistants [RAs]) will meet with families, explain the purpose of the intervention, and provide an overview of the intervention materials. Interventionists will then work with families to identify their three most pressing injury-related challenges, determine which information is most relevant, and help families role-play using these strategies. At two and four weeks after baseline, families in the intervention group will be offered a booster session via phone to discuss use of the Kit, problem-solve difficulties, and apply the Kit to new stressors. Families requiring more intensive support will be referred to other services, as this intervention is not a substitute for psychological treatment. Participants assigned to the waitlist group will receive standard care until they are given access to the Cellie Coping Kit intervention (via mail) after the T3 assessment. Standard care will include family-centered medical care, access to support from child life specialists, and referrals to a social worker, psychologist, and/or psychiatrist if the medical team has concerns about a child’s emotional health. At T3, participants will be provided written instructions on how to use the coping kit (rather than an in-person introduction) and contact information for questions related to the intervention. This group will not receive the booster sessions. Interventionists will complete fidelity measures at T1, booster sessions, and T2 (see Table 1). At 6 weeks (T2), 12 weeks (T3), and 18 weeks (T4) after baseline, participants will repeat T1 measures. In addition, parents will report on adherence at T2 (see Table 1). Children, parents, and a physician (blinded to participants’ condition) will also rate physical recovery at T3. Assessments will be completed via phone or Redcap [43]. It is estimated that participants will complete T1 assessments in approximately 25 min and follow-up assessments in about 20 min. To improve retention, families will be contacted five times each via phone for follow-up assessments. If research assistants are unable to contact families for follow-ups via phone, an electronic link to the follow-up survey on REDCap will be sent via email. If the family does not complete assessments via phone or Redcap [43], families will be asked to complete assessments via mail. The study protocol has been reviewed and approved by the Institutional Review Board at the University of Kentucky and is registered at clinicaltrials.gov. See Fig. 2 for CONSORT diagram [44] and Fig. 3 for the SPIRIT checklist and Addiitional file 1 for SPIRIT checklist.

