
**Table 1 Tab1:** Constructs and measures for RCT

Construct/Measure	Assessment^a^			
Interventionist Report	T1	T2	T3	T4
Fidelity/Fidelity checklist	X (intervention group)	X (intervention group)		
Injury and treatment characteristics/Medical record review/abstraction	X			
Physician report	T1	T2	T3	T4
Physical Injury Recovery			X	
Child Self-Report	T1	T2	T3	T4
Intervention feasibility/Satisfaction Questionnaire [45, 46]		X (intervention group)		X (waitlist group)
Physical Injury Recovery			X	
Coping/How I Coped Under Pressure Scale (HICUPS) [47]	X	X	X	X
Health-related quality of life/Pediatric Quality of Life Inventory (PedsQL) [48]	X	X	X	X
Child and Adolescent Trauma Screen (CATS) [54]	X	X	X	X
Parent Self-Report	T1	T2	T3	T4
Intervention feasibility/Satisfaction Questionnaire [45, 46]		X (intervention group)		X (waitlist group)
Physical Injury Recovery			X	
Adherence/Health Care Questionnaire (HCQ)		X		
Coping Assistance/Parent Socialization of Coping Questionnaire (PSCQ) [47]	X	X	X	X
Health-related quality of life/PedsQL [49, 50]	X	X	X	X
Child Psych Symptoms/Pediatric Symptom Checklist (PSC) [51–53]	X	X	X	X
Child and Adolescent Trauma Screen- Caregiver Report (CATS) [54]	X	X	X	X

^a^Time of assessment: T1 = baseline; T2 = 6 weeks; T3 = 12 weeks; T4 = 18 weeks

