### Sample size

A goal of this pilot RCT is to estimate effect sizes for a full-scale RCT. Within the constraints of a pilot study, we aim to have reasonable power to detect a clinically meaningful effect for mechanisms of action (T2 adherence, coping) and child health outcomes (T3 physical recovery, HRQOL, emotional health symptoms). A sample of *n* = 80 (40 per condition; 68 [85%] retained to T3) can detect a 0.7 effect size between groups at T3 (ANCOVA) with 80% power and α = 0.05. Retention rate will be tracked and considered in designing subsequent research trials.

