### Data analysis

For all analyses, we will include covariates of child age, sex, and injury characteristics (e.g. severity, length of recovery, type of procedures). Missing data will be imputed in cases in which at least 50% of a measure’s subscale is complete; in cases in which > 50% of the items on a given subscale are missing, participants’ will be dropped from analyses requiring those subscales but will be retained in the overall study. Regarding the primary objective, examining intervention feasibility (fidelity, acceptability, implementation, cost), we will perform descriptive statistics that will summarize: (1) fidelity, i.e. when, how, and what parts of intervention were implemented (child, parent, interventionist report), engagement (child, parent, interventionist report); (2) acceptability, i.e. child/parent satisfaction questionnaire and interview data; (3) implementation, i.e. selection of target stressors, strategies used, barriers identified (interview, session data), rate of booster session completion; and (4) cost, i.e. resources required (session time, additional family contact, booster calls, training/supervision, kit costs). We will consider the intervention feasible if: (i) > 50% of the participants in the intervention group report implementing the intervention; and (ii) > 75% of participants who implemented the intervention report high satisfaction with the intervention. Data on what parts of the intervention were used and the cost will inform future intervention development and research.

To determine the intervention’s efficacy and analyze mechanisms of action and health outcomes, our primary analytic approach will be analysis of covariance (ANCOVA) for initial estimation of effect sizes. ANCOVA can adjust for baseline group differences (intervention versus waitlist) if imbalances occur despite randomization. The dependent variable in each ANCOVA will be a follow-up measure (e.g. T2 adherence, coping; T3 HRQOL, psychological symptoms), with corresponding T1 score as the covariate. Thus, we will examine intervention effects at T2 and T3 while controlling for T1 differences (comparing the intervention group to the waitlist group). We will explore mechanisms of actions at T2 as possible mediators of the intervention effect on health outcomes at T3 via multivariable regression analysis. Data collected at T4 will be exploratory and will also be examined using ANCOVAs to allow us to examine potential intervention timing effects.

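### At T4 the start of the kit is completely aliased with the level of interventionist support, so the exploratory T4 contrast cannot be read as a timing effect or as evidence on whether interventionists are necessary

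*Protocol article*

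**What the plan says.** The kit is "introduced to the immediate intervention group after the T1 assessment and to the waitlist group following the T3 assessment" (Abstract, Method / Design). The visit schedule in the footnote to Table 1 is "T1 = baseline; T2 = 6 weeks; T3 = 12 weeks; T4 = 18 weeks".

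The Study design section sets out how each arm receives the kit:

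- **Immediate arm:** a meeting with a trained interventionist, selection of the family's three main challenges, role-play, and telephone boosters offered two and four weeks after baseline.
- **Waitlist arm:** the kit comes by post after T3. At that point "participants will be provided written instructions on how to use the coping kit (rather than an in-person introduction"), with contact details for questions. On boosters: "This group will not receive the booster sessions".

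The protocol makes two statements about what this arrangement can show:

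- **Timing.** Data analysis says that T4 data are exploratory and "will also be examined using ANCOVAs to allow us to examine potential intervention timing effects". The Discussion repeats this as a possibility at T4.
- **Support.** The Discussion says: "The design of this study will allow us to explore whether Cellie interventionists are necessary (Cellie intervention group"). The sentence goes on to the alternative, that families can manage with no further instruction, and gives the waitlist group as the source for that. The same paragraph counts evaluating how much support a family needs among the study's strengths.

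The limitations at the end of the Discussion cover variable usage, retention, recruitment, blinding and pilot size. They do not say that start time and support change together.

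**The concern.** A timing effect is the difference between early and late start with delivery held fixed. The need for interventionists is the difference between supported and unsupported delivery with start time held fixed. The design holds neither fixed, because each arm has one start time and one mode of delivery.

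A T4 difference could therefore come from the earlier start, from the support, or from both. No difference could mean that a mailed kit does as well, that an early start adds nothing, or that both arms have recovered naturally by week 18. The pilot is meant to inform a full-scale trial, and the Discussion links the level of support to roll-out in areas short of professionals. Reading the T4 result as an answer on timing or support could carry an unsupported conclusion into that planning.

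**Working it through.** **The plan's own figure.** The Sample size section says that the sample ("40 per condition; 68 [85%] retained to T3") "can detect a 0.7 effect size between groups at T3 (ANCOVA) with 80% power and α = 0.05". Assuming equal loss, 68/2 = 34 per arm. For a two-sided two-sample comparison of means, n per arm = 2(1.960 + 0.842)²/0.7² = 32.04, rounded up to 33. The t-based calculation gives 33.02 per arm, power 0.812 at 34 per arm, and a detectable effect of 0.690 at 80% power. The figure reproduces. It is stated for T3 and does not bear on what the T4 contrast identifies.

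**The arms side by side at T4 (week 18).**

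| | Immediate | Waitlist |
|---|---|---|
| Kit start | week 0 | week 12 |
| Time since receipt | 18 − 0 = 18 weeks | 18 − 12 = 6 weeks |
| Introduction | in person, with role-play | mailed, written instructions |
| Boosters | 2 offered | 0 |

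Times since receipt are approximate, since the kit follows the T3 assessment by post. Row 2 follows from row 1 once the visit is fixed, so it is not a separate factor. Rows 3 and 4 are both parts of interventionist support. That leaves two dimensions: timing and support.

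**Identification.** Write the T4 mean as μ + τE + σS, where E = 1 for an early start and S = 1 for supported delivery. The immediate arm has E = S = 1 and the waitlist arm has E = S = 0. The between-arm difference is

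Δ = (μ + τ + σ) − μ = τ + σ,

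plus any interaction between the two. The design rows are (1, 1, 1) and (1, 0, 0), so the matrix has rank 2 for 3 columns. Coding all four table rows separately, with an intercept, also gives rank 2, for 5 columns. Either way only one contrast between arms is estimable. For example, Δ = 0.7 fits τ = 0.7 with σ = 0 exactly as well as τ = 0 with σ = 0.7.

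**What cannot break the aliasing.**

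- *Covariates.* The planned T1 score, age, sex and injury characteristics do not help, because E and S are both functions of arm alone.
- *Sample size.* More families make τ + σ more precise but do not divide it.
- *The T3 contrast.* This compares the supported kit with standard care and contains no unsupported delivery.
- *The waitlist arm's change from T3 to T4.* This is mixed with natural recovery over those weeks.
- *Use and satisfaction data.* Table 1 schedules this questionnaire at T2 for the immediate arm (6 − 0 = 6 weeks after receipt) and at T4 for the waitlist arm (18 − 12 = 6 weeks). Time since receipt is matched, but the period covered is weeks 0–6 versus weeks 12–18 after baseline, and support still differs.

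**The case against.** The strongest reply is that the protocol claims little. T4 is labelled exploratory, timing effects are only potential, and the interventionist question is something to explore. Neither question is among the three objectives under Current study. This stands as to weight: a reader might infer that the protocol promises to demonstrate both effects, and its wording does not go that far. But exploratory status lowers the certainty expected of an estimate; it does not make an inseparable effect estimable. The closing caveat that a larger sample is needed does not cover the problem, since size is not the obstacle.

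Second, the Discussion ties only timing to T4 by name; the interventionist sentence refers to the design in general. That is correct. However, the waitlist arm has the kit only after T3, so its only scheduled assessment with the kit is T4, and any comparison of supported with unsupported delivery must draw on it.

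Third, the other half of the interventionist sentence asks whether families can use the kit unaided. The waitlist arm's T4 use and satisfaction data can inform that descriptively, and the limitations paragraph commits to examining usage. This stands in full. A reader might infer that the design says nothing about unaided use; the documents do not support that.

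Fourth, a reader might count four separate confounders. As shown in the working, there are two. Boosters are also offered rather than assured, with completion tracked.

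**Conclusion.** The point holds as a limit on interpretation. At T4, timing and support are completely aliased: one estimable contrast for two effects. The T4 ANCOVA can be reported as a randomised comparison of two packages, but neither a difference nor its absence can be assigned to start time or to interventionists. The limitations should say so and do not.

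This rests only on the delivery schedule in Study design and the visit times in Table 1. It needs no assumption about effect size, retention or variance.

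Its reach is narrow. A reader might infer that the efficacy comparisons are compromised. They are not: at T2 and T3 the waitlist arm is still on standard care, so those contrasts are untouched. Nor does the document say that T4 results will decide whether interventionists are kept in a later trial; that is a risk of misreading, not a stated plan.

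**What to change.** 1. In Data analysis and the Discussion, define the T4 contrast as immediate, interventionist-supported kit versus 12-week-delayed, mailed kit, compared as whole packages. Remove the attribution to timing.
2. In the Discussion, remove the statement that the design can explore whether interventionists are necessary. Keep whether families can use the kit unaided as a descriptive feasibility result from the waitlist arm's T4 use and satisfaction data. Note that setting these beside the immediate arm's T2 data matches time since receipt but is confounded by stage of recovery, as well as differing in support.
3. Add to the limitations that start time and level of support cannot be separated at T4.

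The cost is wording in two sections and two exploratory attributions given up. No change to recruitment, visits, measures or the T2 and T3 analyses is needed. Separating the two effects would take a further randomised arm or a factorial design, which is a matter for the later trial.
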